### 2.2.1 EXEMPTIONS FROM SAE REPORT SUBMISSION

For this trial, the following events are exempt from requiring expedited notification on an SAE Report Form, but must be recorded in the relevant section(s) of the trial CRFs:

- any event that occurs after 30 days post last dose of chemotherapy that is not an ***AE of special interest*** listed in the section above or considered to be causally related to trial treatment
- Elective hospitalisation and surgery for treatment of locally advanced rectal carcinoma or its complications e.g. bowel obstruction
- Elective hospitalisation to simplify treatment or procedures e.g. central line insertion
- disease progression leading to hospitalization, or prolongation of hospitalization, or death as a result of disease progression

**Please note that hospitalisation for elective treatment or palliative care does not qualify as an SAE.**

### 2.3 DETERMINING ADVERSE EVENT EXPECTEDNESS

The following AEs are commonly associated with FOLFOX and CAPOX regimens or with rectal cancer surgery and will be considered expected:

| Expected Adverse Events from Chemotherapy                                                                                                                                                                                                                                                                                                                                                                        |                                                                                                                                                                                                                                                                                                                                                                                                                                                          |
|--------------------------------------------------------------------------------------------------------------------------------------------------------------------------------------------------------------------------------------------------------------------------------------------------------------------------------------------------------------------------------------------------------------------------------|----------------------------------------------------------------------------------------------------------------------------------------------------------------------------------------------------------------------------------------------------------------------------------------------------------------------------------------------------------------------------------------------------------------------------------------------------------|
| 

• Abdominal pain

• Allergic reaction

• Alopecia

• Anaemia

• Anorexia (Grade ≤ 3)

• Cardiac disorders (e.g. arrhythmias, heart failure, ischemia)

• Constipation (Grade ≤3)

• Decreased platelet count

• Dehydration

• Diarrhoea

• Dysaesthesia

• Fatigue

• Febrile neutropenia

 | 

• Fever (Grade ≤ 3)

• Mucositis oral (Grade ≤ 3)

• Nausea

• Neuropathy – peripheral and sensory

• Neutrophil count decreased

• Neutrophil count decreased with infection

• Pain

• Paraesthesia

• Skin NOS (inc. Palmar-plantar erythrodysesthesia syndrome)

• Thromboembolic events (thrombosis and embolism)

• Vomiting

 |
| Expected Adverse Events from Surgery (termed complications)                                                                                                                                                                                                                                                                                                                                                      |                                                                                                                                                                                                                                                                                                                                                                                                                                                          |
| Operative 

• Damage to organ/structure e.g. Bowel/Bladder/Ureter/Major Nerves

• Faecal contamination

• Haemorrhage

 Post-operative                                                                                                                                                                                                                 | 

• Scrotal swelling

• Sepsis

• Sexual dysfunction

• Stoma prolapse/necrosis

• Stroke or Transient Ischaemic Event

• Subcutaneous emphysema

• Urinary dysfunction

                                                                                                                                                                                          |

|                                                                                                                                                                                                                                                                                                                                                                                                                                                                                                                                                                                                                                                                                                                                                                                                                                  |                                                                                                                                                                                                                                                                                                                                                                                                                                                                                                                                                                                                                                                                                                                                                                                              |
|----------------------------------------------------------------------------------------------------------------------------------------------------------------------------------------------------------------------------------------------------------------------------------------------------------------------------------------------------------------------------------------------------------------------------------------------------------------------------------------------------------------------------------------------------------------------------------------------------------------------------------------------------------------------------------------------------------------------------------------------------------------------------------------------------------------------------------|----------------------------------------------------------------------------------------------------------------------------------------------------------------------------------------------------------------------------------------------------------------------------------------------------------------------------------------------------------------------------------------------------------------------------------------------------------------------------------------------------------------------------------------------------------------------------------------------------------------------------------------------------------------------------------------------------------------------------------------------------------------------------------------------|
| 
 
• Acute renal failure
 
• Anastomotic leak
 
• Back pain
 
• Bowel Dysfunction
 
• Cholecystitis
 
• Delirium
 
• Disseminated intravascular coagulation
 
• Distal limb ischaemia/compartment syndrome
 
• Gastrointestinal fistula
 
• Gastrointestinal ischaemia/necrosis
 
• Gastrointestinal obstruction
 
• Gastrointestinal perforation
 
• Gastrointestinal stricture/stenosis
 
• Gastrointestinal ulceration
 
• Haemorrhage
 
• Hernia
 
• Ileus
 
• Intra-abdominal/pelvic abscess
 
• Metabolic acidosis
 
• Pancreatitis
 
• Post-operative peritonitis
 
• Pressure sore
 
• Pseudomembranous colitis
 
 | 
 
• Urinary retention
 
• Urinary tract infection
 
• Wound infection
 
• Wound dehiscence
 
 
Cardiorespiratory (May be operative or post-operative)
 
Respiratory, including
 
 
• Acute respiratory distress syndrome/respiratory failure
 
• Aspiration
 
• Atelectasis
 
• Bronchospasm
 
• Pleural effusion
 
• Pneumonia/chest infection
 
• Pulmonary embolus (or DVT)
 
 
Cardiac, including
 
 
• Arrhythmia
 
• Cardiac failure
 
• Ischaemic heart disease / myocardial infarction
 
• Cardio-respiratory arrest
 
 |
|----------------------------------------------------------------------------------------------------------------------------------------------------------------------------------------------------------------------------------------------------------------------------------------------------------------------------------------------------------------------------------------------------------------------------------------------------------------------------------------------------------------------------------------------------------------------------------------------------------------------------------------------------------------------------------------------------------------------------------------------------------------------------------------------------------------------------------|----------------------------------------------------------------------------------------------------------------------------------------------------------------------------------------------------------------------------------------------------------------------------------------------------------------------------------------------------------------------------------------------------------------------------------------------------------------------------------------------------------------------------------------------------------------------------------------------------------------------------------------------------------------------------------------------------------------------------------------------------------------------------------------------|

For those events not described in the list above or in ***Events of Special Interest*** or ***Exemptions from SAE reporting*** please determine the expectedness and relatedness of an SAE by using the reference safety information included in Section 4.8 (Undesirable effects) of the summary of product characteristics (SmPC) for Capecitabine, 5-FU, Oxaliplatin and Folinic acid. The version of each of the SmPCs approved for this trial is shown in Section 9.4. [An](#) electronic and hard copy of each SmPC will be provided at the time of site initiation and updates sent as necessary.

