## 9.4 SUMMARY OF PRODUCT CHARACTERISTICS

The reference document relating to each of the IMPs listed in section 9.2 is the SmPC. Section 4.8 (Undesirable effects) of the SmPC represents the reference safety information for each of the IMPs, which should be used by investigators as a reference point when assessing causality and expectedness.

| Investigational medicinal product                        | Brand      |
|----------------------------------------------------------|------------|
| Capecitabine 150mg film coated tablet                    | Accord     |
| Capecitabine 500mg Film coated tablet                    | Accord     |
| Fluorouracil 25mg/ml Injection                           | Hospira UK |
| Fluorouracil 50mg/ml Injection                           | Hospira UK |
| Oxaliplatin 5mg/ml Concentrate for Solution for Infusion | Hospira UK |
| Calcium folinate 10mg/ml Injection                       | Hospira UK |

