#### 1.3 UNEXPECTED ADVERSE REACTION (UAR)

An adverse reaction the nature and severity of which is not consistent with the information about the medicinal product in question set out in the Summary of Product Characteristics (SmPC) for that product.

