#### **1.6 SUSPECTED UNEXPECTED SERIOUS ADVERSE REACTION (SUSAR)**

A SUSAR is defined as an adverse reaction suspected to be related to the investigational medical product (the systemic chemotherapy) that is both unexpected and serious.

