**Please ensure that all completed SAE reports are faxed within 24 hours of becoming aware of the event.**

**SAE FAX NUMBER - [name]**

Follow-up of adverse events will continue until all the necessary safety data for the event has been gathered and until the drug-related AE or SAE has either resolved, returned to baseline or stabilised. For fatal or life-threatening cases, follow-up information should be reported as soon as possible. The investigator may be asked to provide follow-up information, discharge summaries, and extracts from medical records as necessary.

Should the investigator become aware of any drug-related SAEs after a patient has been withdrawn from study treatment these must also be reported within the timelines specified above.

The CTIMP Lead and CI (or in nominated individual in their absence) will be responsible for expedited reporting of all SUSARs to the MHRA, REC and Clinical R&D Office no later than 7 calendar days for fatal or life threatening SUSARs, or no later than 15 days for SUSARs which are nonfatal or non-life threatening. Follow up information for death/ life-threatening SUSARs should be provided within 8 days of initial report. For all other SUSARs, follow up report should be provided when the information becomes available.

The Sponsor is also responsible for all submissions of annual reports to the MHRA and REC. Development Safety Update Reports (DSURs) will be prepared in conjunction with the Clinical R&D office.

All SAEs will be reported to the Trial Management Group (TMG) approximately 6-monthly and to the Data Monitoring and Ethics Committee (DMEC) annually.

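### Appendix 1 section 2.3 lets a protocol list, mostly without severity limits, decide expectedness ahead of the SmPC, which contradicts section 9.4 and Appendix 1 section 1.3

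*Protocol*

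**What the plan says.** The protocol speaks to expectedness in three places.

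- **Section 9.4** lists the trial drugs and says that SmPC section 4.8 "represents the reference safety information for each of the IMPs, which should be used by investigators as a reference point when assessing causality and expectedness". It makes no exception for a list elsewhere in the protocol.
- **Appendix 1 section 1.3** defines an unexpected adverse reaction as "An adverse reaction the nature and severity of which is not consistent with the information about the medicinal product in question", as set out in that product's SmPC. Both nature and severity count, and the comparison is with the product concerned.
- **Appendix 1 section 2.3**, the operational section, introduces a two-part table (chemotherapy, then surgery) with "The following AEs are commonly associated with FOLFOX and CAPOX regimens or with rectal cancer surgery and will be considered expected". After the table, the instruction to consult SmPC section 4.8 begins "For those events not described in the list above" and also leaves out events covered by the special-interest and exemption provisions.

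Two further passages give the classification its consequence. Appendix 1 section 1.6 defines a SUSAR as a suspected reaction to the investigational product "that is both unexpected and serious". Under Appendix 1 section 2.4 the CTIMP Lead and Chief Investigator "will be responsible for expedited reporting of all SUSARs to the MHRA, REC and Clinical R&D Office", within 7 days if fatal or life-threatening and within 15 days otherwise.

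**The concern.** Section 2.3 is where a site investigator looks to decide expectedness. For a listed term it gives the answer at once and never reaches the SmPC. Sections 9.4 and 1.3 require the SmPC comparison for every drug-related event, with severity as part of it. One event can therefore be expected under one section and unexpected under another, and the protocol does not say which section prevails.

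Expectedness is what separates a SUSAR from any other serious adverse reaction. If section 2.3 is followed as written, a serious drug-related event that matches a listed term, but is more severe than the SmPC describes or is not described for the drug the patient received, can be classed as expected. It would then lose the expedited report to the regulator and the ethics committee.

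**Working it through.** No sample size, power or error rate is involved. The check compares the two rules and counts the list.

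**1. The two routes.** Take a serious event judged related to the systemic chemotherapy, whose term is on the section 2.3 chemotherapy list with no grade limit.

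- By section 2.3: the term is listed, so the event is expected. It is not a SUSAR, and the 7/15-day report is not triggered.
- By sections 1.3 and 9.4: compare nature and severity with SmPC section 4.8 of the drug given. If consistent, the event is expected. If not, it is unexpected, and being serious and related it is a SUSAR.

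The routes agree only when the listed term, at the severity observed, is consistent with the SmPC of the drug received. Section 2.3 removes the step that would show whether it is.

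**2. Severity limits in the chemotherapy list.** The table has two columns, with 13 and 11 terms: 13 + 11 = 24. Four carry a limit of grade 3 or lower: anorexia, constipation, fever and oral mucositis. That leaves 24 − 4 = 20 without one, and 20/24 = 83%. The 20 include allergic reaction, cardiac disorders as a whole category, thromboembolic events, febrile neutropenia and unqualified pain. Because four terms are capped, the natural reading is that the other 20 are uncapped, so that a grade 4 or 5 event under them is still on the list. Section 1.3 makes severity part of the definition, so the list omits a required element for most of its terms.

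For completeness, the surgical part has 48 entries, none with a grade limit. Together, 20 + 48 = 68 of 24 + 48 = 72 entries (94%) have no severity limit.

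**3. Link to the drug received.** Section 2.3 ties its chemotherapy terms to the FOLFOX and CAPOX regimens. Section 9.2 and Appendix 2 section 1 also allow single-agent capecitabine or 5-FU, and Appendix 2 says this is typically reserved for frail patients. No listed term is attributed to an individual drug. For a patient who never receives oxaliplatin, a listed term is therefore expected under section 2.3 without reference to the SmPC of the drug actually given, whereas section 1.3 refers to the product concerned.

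**4. What else catches the event.** Appendix 1 section 2.4 sends every non-exempt SAE to the sponsor within 24 hours. Appendix 1 section 2 has the Chief Investigator and CTIMP Lead (or delegate) review all SAEs. Section 2.4 also reports SAEs to the TMG about six-monthly and to the DMEC annually. What is at risk is therefore SUSAR classification and the 7/15-day report, not SAE reporting as a whole. No passage says that the central reviewer may set the list aside.

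**The case against.** The strongest reply has four parts.

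**The SmPCs may cover these terms anyway.** If section 4.8 of each SmPC describes every listed term at every severity, the two rules give the same answer. Capecitabine and 5-FU are also components of the listed regimens, so terms on the list may well apply to them alone. The SmPC texts are not in the documents, so no missed SUSAR can be shown. This stands, and it limits the finding to a conflict between rules. It does not remove the conflict.

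**Sections 1.3 and 9.4 remain in force.** Section 9 points readers to Appendix 1 for expected events, so the list may be meant to supplement the SmPC. A reader might infer from section 2.3 that no grade 4 or 5 reaction under the 20 uncapped terms could ever be a SUSAR. The documents do not support that absolute: section 2.3 is not stated to override the other two sections, and a central reviewer applying section 1.3 could reach a different classification. But section 2.3 does not read as a supplement either, since it makes the SmPC conditional on absence from the list.

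**The surgical terms are separate.** A reader might infer that surgical complications such as sepsis or pancreatitis count as expected in a patient who defers surgery and never has an operation, and that these patients are therefore the most exposed. This rests on reading the whole table without its headings. The surgical terms have their own heading, with operative and post-operative subheadings, and Appendix 1 section 2 requires the adverse event form to record relation to chemotherapy or to surgery. Control patients also receive 24 weeks of chemotherapy, after surgery, where attribution is less clear. Neither inference is supported. A clarifying sentence about the surgical list is still worthwhile.

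**SAE reporting continues.** This is correct and has been allowed for above. It reduces the consequence but does not replace the expedited report.

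**Conclusion.** The contradiction is established by the text. Section 2.3 makes listed terms expected and uses SmPC section 4.8 only as a fallback, while section 9.4 and Appendix 1 section 1.3 make the SmPC, by nature and severity, the test. The exposed part is the chemotherapy list: 20 of 24 terms have no severity limit, and none is tied to the drug received. If section 2.3 is followed as written, a serious drug-related event matching a listed term can be classed as expected without an SmPC check and miss the 7- or 15-day report. It would still reach the sponsor as an SAE, unless exempt, and be reviewed centrally.

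The number of events affected cannot be determined from the documents, because it depends on the SmPC texts. The conclusion assumes only that sites apply section 2.3 literally. No trial endpoint or planned analysis depends on expectedness, so this is a safety-reporting correction that should be made, not a threat to the trial's results.

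**What to change.** Reconcile Appendix 1 section 2.3 with section 9.4 and Appendix 1 section 1.3:

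- Remove the clause that makes absence from the list the condition for consulting the SmPC.
- State that, for events related to the trial drugs, expectedness is decided by SmPC section 4.8 of the drug or drugs the patient actually received, by nature and severity.
- Keep the chemotherapy list, labelled as information only.
- As a clarification, state that the surgical list applies only to events attributed to surgery.

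Section 9.4 needs no change of reference.

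The cost is a protocol wording change, a note to sites and possibly a few more SUSAR reports. Central review of all SAEs is already in place, so no new review step is needed.

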## 2.4 NOTIFICATIONS

All SAEs other than those that are exempt from expedited notification (section 2.2.1 above) must be reported to the Sponsor on a completed SAE Report Form within 24 hours of discovery or notification of the event. These must be faxed to Clinical Trials Unit at the Royal Marsden on [name].

**Please ensure that all completed SAE reports are faxed within 24 hours of becoming aware of the event.**

**SAE FAX NUMBER - [name]**

Follow-up of adverse events will continue until all the necessary safety data for the event has been gathered and until the drug-related AE or SAE has either resolved, returned to baseline or stabilised. For fatal or life-threatening cases, follow-up information should be reported as soon as possible. The investigator may be asked to provide follow-up information, discharge summaries, and extracts from medical records as necessary.

Should the investigator become aware of any drug-related SAEs after a patient has been withdrawn from study treatment these must also be reported within the timelines specified above.

The CTIMP Lead and CI (or in nominated individual in their absence) will be responsible for expedited reporting of all SUSARs to the MHRA, REC and Clinical R&D Office no later than 7 calendar days for fatal or life threatening SUSARs, or no later than 15 days for SUSARs which are nonfatal or non-life threatening. Follow up information for death/ life-threatening SUSARs should be provided within 8 days of initial report. For all other SUSARs, follow up report should be provided when the information becomes available.

The Sponsor is also responsible for all submissions of annual reports to the MHRA and REC. Development Safety Update Reports (DSURs) will be prepared in conjunction with the Clinical R&D office.

All SAEs will be reported to the Trial Management Group (TMG) approximately 6-monthly and to the Data Monitoring and Ethics Committee (DMEC) annually.

